where $Z_{1-\alpha /2}$ = 1.96 (corresponding to a two-sided significance level of α = 0.05), $Z_{1-\beta }$ = 0.8416 (corresponding to 80% statistical power), and d = 0.80 (Cohen’s d, representing a large standardized effect size). Substituting these values yields$$n=2{\left(\frac{1.96+0.8416}{0.80}\right)}^{2}=2{\left(\frac{2.8016}{0.80}\right)}^{2}=2{\left(3.502\right)}^{2}=2\left(12.264\right)\approx 25\;\mathrm{per}\;\mathrm{group}$$

This yields a minimum of 25 participants per group. Enrollment was set at 30 per group (*N* = 60 total) to accommodate an anticipated attrition rate of approximately 20%, accounting for incomplete recordings, data quality exclusions, and participant withdrawal while preserving adequate statistical power for the primary analysis.

This study is powered to address the primary aim only. Secondary and exploratory analyses are intended to generate preliminary effect size estimates and variability data to inform future hypothesis-driven studies. Up to 300 individuals may be screened to achieve target enrollment, reflecting the expected distribution of risk classification within the clinic population and anticipated exclusions. A stratified quota sampling approach will be used to ensure balanced representation of each PSQ-defined risk group, a design feature that does not alter the cross-sectional nature of the study but ensures adequate statistical power for between-group comparisons. Participants who discontinue or have incomplete data will not be replaced.

The study was approved by the Institutional Review Board of the University of North Carolina (UNC) at Chapel Hill (IRB#25-3218, 26 January 2026) and registered at ClinicalTrials.gov (NCT07581938, 5 May 2026). Recruitment and follow-up procedures will be conducted between May 2026 and June 2027. This protocol is reported in accordance with the Standard Protocol Items: Recommendations for Interventional Trials (SPIRIT) 2025 statement [36] and adapted accordingly for this prospective, cross-sectional observational study. A completed SPIRIT 2025 checklist is provided as Supplementary Table S1.

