### 2.3. Screening and Eligibility

Children meeting all inclusion criteria and none of the exclusion criteria will be eligible for enrollment. The age range of 8–13 years was selected to capture a developmental period when SDB may influence craniofacial growth and psychosocial functioning while also allowing reliable completion of self-report measures.

Eligible participants will be children aged 8–13 years receiving care at the UNC ASOD Pediatric Dentistry Clinic with an American Society of Anesthesiologists (ASA) Physical Status Classification of I or II. Participants must be able to read and understand English or Spanish, provide assent with parental or guardian consent, and have access to a smartphone compatible with the home sleep monitoring application.

Participants will be excluded if they have a prior diagnosis of SDB or OSA, history of adenotonsillectomy, craniofacial syndromes or conditions known to substantially alter craniofacial morphology, prior or current orthodontic treatment, or prior orthognathic surgery. These exclusion criteria were selected to reduce heterogeneity in upper airway anatomy and SDB risk factors that could confound interpretation of physiologic sleep and craniofacial outcomes.

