### 2.7. Exploratory Craniofacial Assessment

Exploratory craniofacial analyses will be conducted among participants with clinically available lateral cephalometric radiographs obtained as part of routine dental or orthodontic care. No radiographs will be obtained specifically for research purposes, and study participation will not require the availability of a cephalometric radiograph. Clinically obtained lateral cephalometric radiograph within six months prior to or within six months after the baseline study visit or enrollment will be used when available in the electronic medical record. For participants with multiple available radiographs, the image obtained closest to the baseline study visit will be selected for analysis.

Cephalometric measurements will be obtained using standardized landmark identification and tracing procedures by calibrated study personnel. Variables of interest will include dental and skeletal planar values and skeletal vertical and anterior–posterior values relevant to upper airway patency. Because cephalometric imaging will only be available for a subset of participants and was not obtained under a standardized research imaging protocol, these analyses are considered exploratory and hypothesis-generating.

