### 2.9. Statistical Analysis

Descriptive statistics will be used to summarize participant characteristics, clinical measures, psychosocial outcomes, and physiologic sleep parameters. Continuous variables will be reported as means and standard deviations or medians and interquartile ranges depending on distributional characteristics assessed by Shapiro–Wilk tests, while categorical variables will be summarized using frequencies and percentages.

For the primary analysis, physiologic sleep parameters (sAHI, sRDI, SAI, SQI) will be averaged across qualifying recording nights for each participant and compared between PSQ-based risk groups using independent-samples *t*-tests or Mann–Whitney U tests, as appropriate. Night-to-night reliability of physiologic sleep parameters will be assessed using intraclass correlation coefficients (ICCs). Effect sizes will be reported using Cohen’s d and interpreted according to conventional thresholds, with values of approximately 0.20, 0.50, and 0.80 representing small, medium, and large effects, respectively. Sensitivity analyses will be conducted by (1) restricting analyses to participants with three qualifying recording nights; (2) repeating analyses using only the first qualifying night for each participant; and (3) exploring the inclusion of participants with only one qualifying recording night using the single available recording. Multivariable linear regression models will be used to examine associations between SDB risk classification and physiologic sleep measures while adjusting for prespecified covariates including age, sex, and BMI percentile. Additional covariates (asthma, ADHD) will be included if baseline group differences are identified or if they demonstrate meaningful associations with primary outcomes.

Secondary analyses will evaluate associations between SDB risk classification and psychosocial measures (RCADS-25 scores, PSS-C scores, CRSP-S scores) and BMI using linear regression models. Ordinal outcomes (Mallampati classification, Brodsky tonsillar grade) will be analyzed using Mann–Whitney U tests or ordinal logistic regression, as appropriate.

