Exploratory craniofacial analyses will be conducted among the subset of participants with available lateral cephalometric radiographs. Cephalometric measurements will be summarized descriptively and compared between risk groups using independent-samples *t*-tests or Mann–Whitney U tests. Given the anticipated smaller sample size and exploratory nature of these analyses, findings will be reported as effect size estimates with 95% confidence intervals to inform future study design.

No formal adjustment for multiple comparisons will be applied to secondary and exploratory analyses, as these are intended to generate preliminary estimates rather than confirmatory conclusions. All statistical analyses will be performed using SPSS (v. 31, IBM SPSS Statistics, IBM Corp., Armonk, NY, USA). Statistical significance will be evaluated using two-sided tests with an α level of 0.05.

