## Figures and Tables

**Figure 1 mps-09-00115-f001:**
[figure not shown]
Participant workflow for multimodal sleep-disordered breathing risk assessment. Following screening and enrollment, participants complete baseline clinical, airway, and psychosocial assessments and are classified as low-risk or high-risk for SDB based on Pediatric Sleep Questionnaire (PSQ) scores. Participants then complete a minimum of three consecutive nights of home sleep monitoring using the SleepImage Ring, with adherence check-ins at approximately one and two weeks. Study participation concludes after device return and verification of data completeness. Exploratory cephalometric analyses are performed for the subset of participants with clinically available lateral cephalometric radiographs. Abbreviations: PSQ = Pediatric Sleep Questionnaire; RCADS-25 = Revised Children’s Anxiety and Depression Scale–Short Version; PSS-C = Perceived Stress Scale for Children; CRSP-S = Children’s Report of Sleep Patterns Sleepiness Scale; BMI = body mass index; PCP = Primary Care Provider; sAHI = software-derived Apnea-Hypopnea Index; sRDI = software-derived Respiratory Disturbance Index; SAI = Sleep Apnea Indicator; SQI = Sleep Quality Index; SDB = sleep-disordered breathing.

**Table 1 mps-09-00115-t001:** Schedule of study assessments by study phase.

Study Timepoint	Study Activity	Screening Enrollment	Visit #1 (Baseline)	Home Sleep Monitoring	Visit #2
Enrollment	Eligibility screening	X			
	EHR review	X			
	Informed consent	X			
	Child assent	X			
	HIPAA authorization	X			
	Demographics & Medical history		X		
Clinical Values	BMI		X		
	Mallampati score		X		
	Brodsky score		X		
Classification	PSQ (Parent-reported)		X		
	PSQ scoring risk classification		X		
	Parental notification of PSQ risk status		X		
Participant-reported Outcomes	RCADS-25		X		
	PSS-C		X		
	CRSP-S		X		
Device Distribution	Wearable device fitting & instructions		X		
Follow-Up	Adherence Check-In Calls (Weeks 1 and 2)			X	
Sleep Parameters	sAHI			X	
	sRDI			X	
	SAI			X	
	SQI			X	
	Parental notification of device-derived risk status			X	
Exploratory Outcomes	Cephalometric Analysis		X *		
Study Completion	Device return				X

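### Craniofacial differences in growing children aged 8–13 are estimated without adjustment for age or sex, and the radiograph window admits images taken after parents are told the risk result

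*Protocol article*

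**What the plan says.** - **Craniofacial analysis (Section 2.9).** "Cephalometric measurements will be summarized descriptively and compared between risk groups using independent-samples" t-tests or Mann–Whitney U tests. On the purpose: "findings will be reported as effect size estimates with 95% confidence intervals to inform future study design".
- **Sleep analysis (same section).** The regression models for the physiologic sleep measures are described as "adjusting for prespecified covariates including age, sex, and BMI percentile". No such list is given for the craniofacial measurements.
- **Groups (Section 2.1).** "A stratified quota sampling approach will be used to ensure balanced representation of each PSQ-defined risk group". No matching or quota on age or sex is stated.
- **Age band (Section 2.3).** "The age range of 8–13 years was selected to capture a developmental period when SDB may influence craniofacial growth and psychosocial functioning". The same section excludes children with prior or current orthodontic treatment at entry.
- **Radiographs (Section 2.7).** Only clinically obtained images are used, taken "within six months prior to or within six months after the baseline study visit or enrollment". Where a child has several, the one nearest to baseline is taken, on either side.
- **Notification (Table 1 and Section 3.4).** The row "Parental notification of PSQ risk status" is marked at Visit 1. Section 3.4 describes telling the parents of high-risk children, giving them educational material and recommending follow-up with primary care or sleep medicine. It also says that routine dental care is not changed by participation.
- **Acknowledged limit (Section 4).** The radiograph subset is expected to be orthodontically indicated, and group differences are to be read with that selection in mind.

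**The concern.** Skeletal and dental dimensions change with age and differ by sex in children who are still growing. If high-risk and low-risk children with radiographs differ in mean age or sex mix, a crude difference carries part of that gap. The plan treats age and sex as worth adjusting for when the outcome is sleep, but leaves them out where the outcome is growth itself.

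The second part concerns which images enter. A radiograph taken after Visit 1 is taken after the families of high-risk children have been informed. If that prompts imaging in one group more than the other, and imaging also depends on craniofacial form, the two radiograph subsets are no longer comparable. Orthodontic treatment is an exclusion at entry, but Section 2.7 does not say whether an image taken after treatment has started is still used.

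What is at stake is the stated product of this analysis: effect sizes that a later study would take as planning inputs.

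**Working it through.** The article gives no figure for the craniofacial comparison, so there is none to reproduce. Its sample size of 25 per group concerns the primary aim only and does not bear on this point.

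**1. Age confounding**

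Assumed inputs:
- Ages uniform from 8.0 to just under 14.0 years, so the SD is 6/√12 = 1.73 years. The age range comes from Section 2.3; the uniform shape is an assumption.
- Correlation r between age and the measurement of 0.3–0.5. The article gives no value.

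Shift in d = r × (mean age gap) / (age SD).

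- One-year gap, r = 0.3: 0.3 × 1/1.73 = 0.17.
- One-year gap, r = 0.5: 0.5 × 1/1.73 = 0.29.
- Wider range: gap 0.5 year with r = 0.2 gives 0.2 × 0.5/1.73 = 0.06; gap 1.0 year with r = 0.6 gives 0.6 × 1/1.73 = 0.35.

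Section 2.9 treats d of about 0.20 as small and 0.50 as medium, so a shift of this size can move an estimate towards the next category. The effect of a sex imbalance is not quantified here.

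**2. Precision, for scale**

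The number of radiographs is not given. Near d = 0 the 95% CI half-width is about 1.96 × √(2/n), with n per group:

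| n per group (assumed) | Half-width of d |
|---|---|
| 8 | 0.98 |
| 10 | 0.88 |
| 15 | 0.72 |
| 30 | 0.51 |

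**3. Cost of adjusting**

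Take 10 per group (N = 20), two covariates, normal covariates, and sex unrelated to the measurement. The variance of the adjusted difference relative to the crude one is about (1 − r²) × (1 + 2/15), where 15 = 20 − 2 − 2 − 1.

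- r = 0.3: 0.91 × 1.133 = 1.03, so no gain.
- r = 0.5: 0.75 × 1.133 = 0.85, a modest gain.

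The reason to adjust is therefore comparability, not precision.

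**4. Differential imaging**

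This is an illustration with no true group effect. A radiograph is taken when a trait correlated ρ with the measurement exceeds a threshold, and the threshold differs by group. Radiographs are assumed in 20% of low-risk children.

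| ρ | 30% of high-risk imaged | 60% of high-risk imaged |
|---|---|---|
| 0 | 0 | 0 |
| 0.3 | −0.08 | −0.23 |
| 0.5 | −0.13 | −0.42 |

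The entries are spurious d. It is zero when the imaging fractions are equal or when imaging is unrelated to form. The article gives neither the fractions nor ρ.

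**The case against.** The strongest reply is that this is an exploratory analysis, labelled as hypothesis-generating, with confidence intervals and an explicit warning about selection. That stands as far as impact goes: at 10 per group a half-width of 0.88 is about three times the largest one-year shift of 0.29. It does not answer the age and sex point. Section 4 mentions neither, and an interval around a crude difference does not correct a systematic gap.

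A second reply is that an age gap arising by chance is sampling error, which the planned interval covers on average. This is right. At 10 per group the standard error of a chance age gap is 1.73 × √(2/10) = 0.77 year, so sizeable gaps can arise without any bias. Systematic confounding needs age or sex to be associated with questionnaire class in this clinic, and the article does not show that.

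Third, the features that Section 4 takes from a meta-analysis are angles, and the assumed correlations may not fit them equally. The shift scales with r, so a weaker correlation gives a smaller one.

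A reader might infer that the radiographs are taken because families were told the result. The documents do not support that. The window covers the six months before baseline as well, the share of later images is not given, notified families are directed to primary care or sleep medicine rather than to a dentist, and Section 3.4 says routine dental care is unaltered. That last statement is an intention, and the same section expects notification to increase referral and follow-up, so the pathway stays open but is not demonstrated.

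**Conclusion.** The concern holds as a risk, not as a demonstrated bias. The planned craniofacial comparison is unadjusted, in non-randomised groups of growing children, while the same plan adjusts the sleep outcomes for age and sex. If the groups differ by one year in mean age, d shifts by 0.17–0.29, given an age SD of 1.73 years and r = 0.3–0.5, all assumed. With no age or sex difference there is no confounding from this source.

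The window admits images taken after notification and does not exclude images taken after orthodontic treatment starts. Selection that differs by group is therefore possible, and Section 4 discloses only selection of a general kind. Its size cannot be derived from the article.

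The point is minor. It affects the usefulness of the exploratory effect sizes for later planning and leaves the study's main conclusions untouched.

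**What to change.** 1. In Section 2.9, report each craniofacial difference from a linear model with questionnaire class, age at radiograph and sex, with its 95% CI, beside the planned unadjusted estimate.
2. Report by risk group how many children have a usable radiograph and when it was taken relative to baseline.
3. Add a sensitivity analysis limited to radiographs taken on or before the baseline visit. Apart from any taken later that same day, these precede notification, and the entry exclusion means that orthodontic treatment had not begun by then. Keeping this as a sensitivity analysis avoids shrinking the main comparison.

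Cost: wording only, since age, sex and image date come from records the study already uses. The model spends two degrees of freedom in a small subset, with little or no gain in precision if the age correlation is weak, and the restricted subset in step 3 may be too small for more than a descriptive check.

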### 2.10. Data Management and Confidentiality

Study data will be collected and managed using the Research Electronic Data Capture (REDCap), a secure, web-based data management platform hosted by UNC. REDCap provides audit trails for data entry and modification, role-based access controls, and encrypted data storage. Built-in validation features, including range checks and required field prompts, will be used to minimize data entry errors. Periodic data quality reviews will be conducted by study personnel to identify missing or inconsistent entries.

Participants will be assigned unique study identification numbers at enrollment. A master linking file connecting study identification numbers to participant identifiers will be stored separately from study data on a password-protected, encrypted institutional server accessible only to authorized study personnel approved by the IRB. All study data, including questionnaire responses, clinical assessments, and physiologic sleep data, will be linked using study identification numbers rather than personal identifiers.

Physiologic sleep data collected through the wearable home sleep monitoring device will be transmitted through a secure, HIPAA-compliant platform and incorporated into the REDCap database following completion of the monitoring period and quality review. All electronic data will be stored on secure institutional servers in accordance with UNC policies governing research involving human participants.

No formal interim analyses are planned. As this is a non-interventional, observational feasibility study with no therapeutic interventions, formal stopping rules for efficacy or futility are not applicable. The principal investigator will have access to all accumulating data and will make the final decision regarding study continuation or termination, in consultation with the investigative team and the IRB as appropriate.

Research records will be retained for a minimum of 3 years following study completion, in accordance with UNC Office of Human Research Ethics policy and Title 45, Part 46 of the Code of Federal Regulations (45 CFR 46.115). Signed HIPAA authorizations will be retained for a minimum of 6 years. De-identified data may be made available to qualified investigators upon reasonable request and in accordance with applicable institutional and regulatory requirements. All study procedures will be conducted in accordance with applicable federal regulations, institutional policies, and the approved Institutional Review Board protocol.

## 3. Procedure

### 3.1. Participant Workflow and Study Timeline

This study consists of four phases: screening and enrollment, baseline assessment, home sleep monitoring, and study completion. Potentially eligible participants are identified through a review of pediatric dentistry clinic schedules and electronic health records. Following confirmation of eligibility and completion of informed consent and assent procedures, participants complete baseline clinical, airway, and psychosocial assessments as described in Section 2.4 and Section 2.6. Parents or guardians complete the PSQ, and participants are classified as low- or high-risk for sleep-disordered breathing based on established scoring thresholds (Section 2.4). Following completion of baseline assessments, participants receive a wearable home sleep monitoring device and standardized instructions for use (Section 2.5). Participants are instructed to wear the device during sleep for a minimum of three consecutive nights within the following three weeks. Brief telephone contacts are conducted approximately one and two weeks following device distribution to support adherence and address technical questions. Study participation concludes after completion of home sleep monitoring, device return, and final review of study procedures. Figure 1 illustrates the participant workflow, and Table 1 summarizes the schedule of study assessments.

### 3.2. Baseline Assessment Procedures

All baseline assessments are completed during a single study visit coinciding with the participant’s scheduled dental appointment. The visit proceeds in the following sequence: (1) confirmation of parental consent, HIPAA authorization, child assent, and eligibility; (2) collection of demographic and medical history information through medical record review and participant report; (3) parent or guardian completion of the PSQ, which is used to classify participants into low- and high-risk SDB groups; (4) anthropometric measurements (height, weight, BMI calculation); (5) intraoral airway assessments (Mallampati classification and Brodsky tonsillar grading) performed by trained and blinded study personnel; and (6) electronic administration of psychosocial questionnaires (RCADS-25, PSS-C, CRSP Sleepiness Scale) completed by the participant. Detailed descriptions of each assessment instrument, scoring procedures, and psychometric properties are provided in Section 2.4 and Section 2.6. Following completion of all baseline assessments, participants receive the home sleep monitoring device and standardized instructions for use.

### 3.3. Home Sleep Monitoring Procedures

Following device distribution, participants and their parents or guardians are oriented to the SleepImage Ring, including device placement, nightly charging, and synchronization with the accompanying smartphone application. Participants are instructed to maintain their usual sleep routines throughout the monitoring period. To accommodate scheduling conflicts, missed nights, or device return delays, participants are permitted up to three weeks to complete the required minimum of three consecutive nights of monitoring. Research personnel conduct brief adherence check-in telephone calls approximately one and two weeks after device distribution to address technical concerns, encourage compliance, and answer participant questions. No additional study assessments are administered during these calls. Following completion of home sleep monitoring by the first 10 participants, a planned data quality review will be conducted to evaluate potential technical or operational issues, such as device functionality, data completeness, signal quality, successful data transmission, and adherence to the monitoring protocol. Any necessary procedural modifications will be documented prior to continuation of enrollment. Following completion of monitoring, physiologic sleep data will undergo quality assessment for signal quality and completeness prior to extraction of study outcomes; only recordings meeting prespecified quality criteria on at least two nights (average signal quality ≥ 50%, minimum sleep duration ≥ 4 h per night) are included in analyses. Device specifications and physiologic sleep outcome variables are described in Section 2.5.

